### Secondary outcomes

Secondary outcomes are divided into adherence to the activity level (activity diary), performance-based physical function (2MWT), self-reported physical function (KOOS), quality of life (SF-36) and healthcare use.Adherence to the activity level measured with the activity diary

Activity level was defined as the type of activities performed and the time spent on it. Because of the absence of a valid and reliable activity-level questionnaire for patients after a TKA an activity diary was developed. The activity diary focuses on physical activities and there is low burden to administer. Every day patients report which activities they have performed and for how many minutes. Walking, cycling, exercises, walking up and down stairs, household chores, pastime and leisure activities, work and sports activities are mentioned in the activity diary and the patient has the opportunity to note other activities and the time spent on them. Other authors used similar activity diaries in healthy adults [36–38]. The activity diary must be filled out one week preoperatively, during the home-based exercise program, in the sixth week, in the third month and one year after surgery (during one week). The minutes spent on each type of activity will be compared to the recommended time per activity as defined in the home-based exercise program (Table 1) to calculate the percentage of adherence (this can be lower or higher than 100%).Performance-based physical function measured with the 2MWT

The 2MWT measures walking speed. The outcome is the distance in meters. The 2MWT record on a smooth floor with sufficient walking space over a distance of 10 m. The measurements take place at the patients’ home and therefore 10 m was determined as standard because this is the maximum available space at home. The patients have to walk as many meters as possible in two minutes. They are allowed to use a walking aid [39]. The 2MWT is performed after two and six weeks and three months. During the preoperative 2MWT the Gait Analysis List Nijmegen is used to measure the quality of the gait pattern.Self-reported physical function, measured with the Knee Osteoarthritis Outcome Score (KOOS)

The KOOS assesses function over the previous week and is composed of five subscales: pain, symptoms, activities in daily living, activities in sports and leisure, and knee-related quality of life [40–43]. Answers are given using a Likert scale ranging from 0 to 4. A normalized score (100 indicates no symptoms, and 0 indicates extreme symptoms) is calculated for each subscale. The KOOS has been shown to have excellent reliability and good content and construct validity when used for short- and long-term follow-up of knee injury [42, 43]. It has been validated for people with TKA and has been used to evaluate physical therapy outcomes [42, 43]. The KOOS is scored after two and six weeks, three months and one year.Quality of life (QoL), measured with the Short Form 36 (SF-36)

The SF-36 is a multipurpose, short-form health survey with 36 questions that measure eight domains of QoL (vitality, physical functioning, bodily pain, general health perceptions, physical role functioning, emotional role functioning, social role functioning and mental health). It has been shown to capture improvements in seven of its eight domains in patients after TKA in the first three months after surgery [44] and continues to indicate improvements in health-related QoL over the next six months [45]. In addition, the results of the eight domains have been combined into two summary scores: physical component score and mental component score [46]. The SF-36 is scored after two weeks, six weeks, three months and one year postoperatively.Healthcare use

Healthcare use includes all kinds of healthcare consumed by the patient in relation to TKA surgery beginning at the start of the home-based exercise program up to one year postoperatively. It includes physical therapy, hospital visits, visits of the general practitioner and medication use. The patient sign informed consent to ask for an overview of healthcare costs (health insurance, physical therapist) and patients report how much pain medication (paracetamol, NSAIDs) they use for their knee pain. The use of pain medication is asked about through a medication diary. Healthcare use is measured during the period up to one year after surgery.Adherence to the home-based exercise program (intervention group) measured with the accelerometer (activity coaching system)

The accelerometer is only used by patients in the intervention group. The 3D accelerometer is the sensor used by the activity coaching system to register activity levels [27]. The outcome of the accelerometer data are outlined above and shown in Fig. 2. The activity level per day in counts per minute (final point of the blue line in Fig. 2) will be compared to the reference activity line per day in counts per minute (final point of the green line) to calculate the percentage of adherence (this can be lower or higher than 100%). Wearing the accelerometer (adherence to the accelerometer) is determined by asking the patient to report the time of the start and end of wearing the activity coaching system on a form. This is checked with the data on the activity coaching system. The accelerometer and the activity diary are both assessments of physical activity [47].

### Process evaluation

We used a mixed-methods approach in the process evaluation: a quantitative comparison between the activity diary (type and duration of activities performed) and the accelerometer data, and interviews to gain insight into the experiences of patients.

### Interviews

Every third patient who receives the activity coaching system will be asked to participate in a qualitative semi-structured interview to determine the usability of the activity coaching system. Semi-structured interviews with the patients will be conducted three months after surgery. The interviews will take place at the patients’ home and the duration of the interview is at most 30 min. The interviews will be conducted by an independent researcher not involved in the measurements or treatments to guarantee independence. Inclusion of patients will be stopped if saturation is reached (no new information in the last three interviews).

### Sample size

The sample size is based on the primary outcome measure TUG. The sample size is determined using a longitudinal regression model with three follow-up measurement points (two and six weeks and three months). According to the formula described by Twisk [48] for longitudinal studies with repeated measures the required sample size is calculated assuming a mean effect of 10% difference for the TUG scores between the groups over time and a standard deviation of 4.2. These parameter values are based on a study by Kennedy et al. on the clinimetric properties of the TUG in patients with knee and hip arthroplasty [35]. We further assume a correlation coefficient of 0.4 for the correlation between the follow-up measurements. Assuming a dropout rate of 15% a total number of 110 patients is needed. The recruitment period is from 1 April 2015 to 1 August 2017.

### Statistical analysis

#### Patient characteristics

Data will be analyzed with the IBM Statistical Package for the Social Sciences (SPSS) version 22. Patient characteristics at baseline will be analyzed anonymously and compared using measures of central tendency and dispersion (mean, standard deviation, median and range) for continuous variables and percentages for dichotomous variables.

#### Primary and secondary outcomes

The analyses will be performed following the intention-to-treat principle. Between-group differences of the primary outcome measure (TUG) measured at baseline, two weeks, six weeks and three months will be analyzed using generalized estimating equations (GEE) with an exchangeable correlation structure. GEE is a longitudinal data analysis technique that is suitable for investigating the course over time of the outcome variable and comparing this overall effect between study arms [49, 50]. Because GEE can adequately handle missing values (<20%), no imputation technique is planned on beforehand.

The continuous secondary outcomes adherence to the activity level, 2MWT, KOOS, SF-36 and healthcare use will be analyzed in the same way using GEE as well.

Differences in the baseline measurements and baseline characteristics of the two groups could potentially act as confounders. Only when the regression coefficient of the intervention variable in the GEE model changes by at least 10% after adding these variables to the model will they be adjusted for in the analyses [48]. A *p* < 0.05 is considered statistically significant. Patients cannot be deprived from other kinds of care and exercises. Therefore, other types of care and exercises are registered and reported.

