### Procedures and informed consent

All eligible patients are informed about this study and are invited to participate by the orthopedic surgeon before surgery. The surgeon informs the researcher about patients possibly willing to participate. The researcher informs the patients by phone about the study and provides them with a patient information letter. Patients have one week to consider participating in the study. Patients who are willing to participate sign an informed consent form. After that, the researcher performs the preoperative measures and determines whether the patient is eligible. To minimize the patients’ load, the preoperative assessment is used as an inclusion criterion and preoperative measurement using overlapping tests. Five orthopedic surgeons perform the TKA surgeries. The number of TKA surgeries per year carried out by each surgeon varies from 50 to 70. After surgery, the definitive inclusion takes place if patients are going home after three days post-surgery and no complications are present. After the definitive inclusion, the baseline measurement and randomization take place. The baseline measurement is planned preferably for the third day, and at the latest for the fifth day. A flow chart is shown in Fig. 1. Subjects can leave the study at any time for any reason if they wish to do so without any consequences. The researcher will report serious adverse events to the accredited medical ethical review board of the Medisch Spectrum Twente community hospital in Enschede, the Netherlands, which approved the trial (registration number P15–09, NL52370.044.15). The researcher can decide to withdraw a patient during the study for urgent medical reasons, such as thrombosis, infections of the knee or other complications. KH is the coordinator of the trial and the other authors comprise the steering committee.

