### Baseline characteristics of participants

Evaluation of baseline characteristics provides insight into the generalizability of the study, the success of the randomization and any potential confounders. Baseline characteristics of participants collected preoperatively are: age (years), gender, BMI, activity level (activity diary), coping style (PAM), walking pattern (GALN), physical status (TUG, 2MWT, KOOS) and quality of life (SF-36). This is shown in the flow chart (Fig. 1).

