### Primary outcome

The primary outcome is the between-group difference in physical functioning as measured by the TUG after two weeks, six weeks and three months. The TUG measures the time it takes a patient to rise from an armchair (seat height of 46 cm), walk 3 m, turn, and return to sitting in the same chair without physical assistance [34]. Patients are instructed to walk safely, but as fast as they can. This test has excellent interrater (ICC 0.97) and intrarater reliability (ICC 0.96), as measured in a group of 65 subjects (aged 45–70) with knee osteoarthritis [34]. The TUG has also been shown to be responsive to change after TKA [35]. The TUG is recorded twice and the highest score of the two measurements is analyzed.

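### The primary GEE is written with baseline TUG in the outcome series and one intervention coefficient; unless a group-by-time term is included, that coefficient is three quarters of the follow-up effect

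*Protocol article*

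**What the plan says.** All references are to the protocol article.

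- **Primary outcome section:** "The primary outcome is the between-group difference in physical functioning as measured by the TUG after two weeks, six weeks and three months". Under Objective, the same three visits are named.
- **Sample size:** based on a "longitudinal regression model with three follow-up measurement points (two and six weeks and three months".
- **Primary and secondary outcomes (Statistical analysis):** "TUG) measured at baseline, two weeks, six weeks and three months will be analyzed using generalized estimating equations (GEE". An exchangeable working correlation is specified, and the technique is said to suit "investigating the course over time of the outcome variable and comparing this overall effect between study arms". The same section describes the intervention coefficient in the singular and applies a 10%-change rule to it. Under that rule, group differences in baseline measurements may be adjusted for as confounders. Continuous secondary outcomes are to be analysed in the same way.
- **Procedures and informed consent:** "After the definitive inclusion, the baseline measurement and randomization take place". This measurement is planned for day 3, and day 5 at the latest. Under the randomization and activity coaching sections, the envelope is opened with the physical therapist at the start of the home program, and the device is worn only during that program.
- **Baseline characteristics of participants:** "Baseline characteristics of participants collected preoperatively are", followed by a list that also contains the TUG.

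**The concern.** The outcome definition and the sample size rest on three visits, while the analysis section lists four. The fourth precedes the intervention, so randomization makes its expected group difference zero, whether baseline means the preoperative or the day 3-5 test.

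The text points to one overall coefficient and mentions no group-by-time term. An analyst who follows the words literally would fit group plus visit to four TUG values. The group coefficient would then mix three visits that can show an effect with one that cannot. The published difference in seconds would be too small, and the test would not be the one for which the trial was sized.

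The section also allows baseline measurements in as covariates under the 10%-change rule. Baseline TUG could therefore be outcome, covariate or both, and the choice would be left until the data are in hand.

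**Working it through.** **1. The dilution factor.** With complete data, equal visit weights (exchangeable structure) and no group-by-time term, the group coefficient is the mean of the visit differences. With differences 0, d1, d2, d3:

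(0 + d1 + d2 + d3)/4 = 3/4 × (d1 + d2 + d3)/3

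This holds for any pattern of d1 to d3 and does not depend on SD, correlation or power.

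**2. With dropout.** Let 15% drop out, 5% after each of baseline, two weeks and six weeks. Under an exchangeable correlation of 0.4, each observation of a patient seen k times has weight 1/(1 + 0.4(k − 1)).

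- Weight on baseline: 0.05/1 + 0.05/1.4 + 0.05/1.8 + 0.85/2.2 = 0.500
- Total weight: 0.05×1/1 + 0.05×2/1.4 + 0.05×3/1.8 + 0.85×4/2.2 = 1.750
- Share of the effect kept: 1 − 0.500/1.750 = 0.71

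**3. The plan's own sample size.** The stated inputs are SD 4.2, correlation 0.4 between follow-ups, three visits, 15% dropout, 110 patients and significance level 0.05 (two-sided assumed). Neither the power nor the mean TUG behind the 10% is stated, so 110 cannot be reproduced from stated inputs alone. It can only be solved backwards:

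- Evaluable: 110 × 0.85 = 93.5, or 46.75 per arm (about 47).
- Variance factor for three visits: (1 + 2×0.4)/3 = 0.60.
- Detectable difference: √[2 × (1.96 + z)² × 4.2² × 0.60 / 46.75] = 1.89 s at 80% power or 2.18 s at 90%. As 10% of a mean, these imply a mean TUG of about 18.9 s or 21.8 s.

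**4. Power with and without baseline in the series.** SE = √(2 × 4.2² × factor/47) and power = Φ(effect/SE − 1.96). The difference that gives 80% power is 1.88 s with 47 per arm. Baseline is assumed to have the same SD and the same correlation of 0.4.

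| Model | Factor | SE (s) | Expected coefficient (s) | Power |
|---|---|---|---|---|
| Three follow-ups | 0.60 | 0.671 | 1.88 | 80% |
| Four visits, group main effect only | (1 + 3×0.4)/4 = 0.55 | 0.643 | 0.75 × 1.88 = 1.41 | 59% |
| Three follow-ups, baseline as covariate | 0.60 − 0.4² = 0.44 | 0.575 | 1.88 | 90.5% |

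If the trial was sized at 90% power (2.175 s with 47 per arm), the four-visit coefficient is 1.63 s and power is Φ(1.63/0.643 − 1.96) = 72%.

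To restore the sized power under the four-visit model, N would have to rise by 0.55/0.60/0.75² = 1.63. That is about 152 evaluable patients, or 179 with 15% dropout.

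**5. Range for the baseline correlation r.** The four-visit factor is (4 + 6×0.4 + 6r)/16 and the covariate-adjusted factor is 0.60 − r². At 1.88 s:

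| r | Four-visit factor | Four-visit power | Adjusted factor | Adjusted power |
|---|---|---|---|---|
| 0.2 | 0.475 | 66% | 0.56 | 83% |
| 0.4 | 0.55 | 59% | 0.44 | 90.5% |
| 0.6 | 0.625 | 54% | 0.24 | 99% |

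**6. GEE simulation.** This used 300 runs, 47 per arm, a true effect of −1.885 s and an exchangeable structure.

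| Model | Mean estimate (s) | Rejection |
|---|---|---|
| Four visits, group main effect | −1.44 | 62% |
| Three follow-ups | −1.92 | 84% |
| Four visits, group-by-post, common baseline mean | −1.91 | 91% |
| Four visits, group plus group-by-post | −1.91 | 70% |
| Three follow-ups, baseline covariate | −1.91 | 91% |
| Four visits, baseline also a covariate | −1.43 | 91% |

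The first two rows give a ratio of 0.75. With 15% monotone dropout they become −1.29 and −1.84, a ratio of 0.70, in line with step 2.

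**The case against.** The strongest reply is that the article does not write out the model. A reader might infer that the plan shrinks the effect by a quarter as a matter of fact, but the text does not support that. It speaks of the course over time and excludes no group-by-time term, and such a term removes the dilution. Exact model terms are also commonly left to a full protocol or analysis plan. This part of the reply stands, so the claim is conditional.

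It can also be said that the four time points only list when TUG is collected, with baseline meant as an adjuster. The outcome definition and the confounder paragraph fit that reading. The sentence itself, however, names the four measurements as what GEE will analyse. Nor does a full group-by-time model sit easily with the text, because it gives visit-specific effects and leaves "comparing this overall effect between study arms" and the 10%-change rule without their single coefficient.

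A reader might infer a certain loss of power. That is not established either. Power and reference mean are unstated, and the correlation of 0.4 is given only for follow-up measurements. If baseline TUG were both outcome and covariate, the estimate would still be cut by a quarter but power would not be lost (91% in simulation).

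Finally, a reader might conclude that baseline has two conflicting definitions. The article largely separates the day 3-5 baseline measurement from preoperative baseline characteristics, and the flow chart is not shown. What remains is that TUG is listed preoperatively too, so the analysis should name the occasion.

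**Conclusion.** The point holds in conditional form. The analysis section puts baseline TUG in the analysed series and refers to one intervention coefficient, which conflicts with the three-follow-up outcome and sample size. Unless a group-by-time or group-by-post term is included, which the text does not state, the coefficient is 3/4 of the follow-up effect with complete data and about 0.70 with 15% monotone dropout.

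The 3/4 factor is plain arithmetic. The power figures (80% to about 59%, or 90% to about 72%) are illustrations. They rest on an assumed design power, a back-solved difference, two-sided testing, 47 evaluable per arm, and baseline sharing the SD of 4.2 and correlation of 0.4. The primary analysis should not stay open to readings whose estimates differ by a quarter.

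**What to change.** Reword the primary analysis before outcome data are compared by arm:

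- **Outcomes:** only the two-week, six-week and three-month TUG.
- **Terms:** group, visit as a categorical factor, and one baseline TUG. The group coefficient is the primary effect.
- **Baseline:** name the occasion. The day 3-5 baseline measurement is the natural choice, using a value recorded before the envelope is opened. Pre-specify it as a covariate and take it out of the 10%-change rule.
- **Acceptable equivalent:** keep baseline in the series, but constrain the arms to a common baseline mean and read the effect from a group-by-post term. The constraint matters. With a free baseline difference the estimate is not diluted, but simulated rejection was 70% against 91%.
- **Secondary outcomes:** use the same model wherever a baseline value exists, such as 2MWT, KOOS and SF-36, naming the occasion for each.

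The cost is a few sentences in the analysis section, with no new visits, patients or data. If the full analysis plan already contains such a model, the article's wording should be aligned with it.

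### Randomized patients may be withdrawn for complications, and the under-20% rule offered for GEE does not protect the intention-to-treat TUG comparison if that loss differs by arm

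*Protocol article*

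**What the plan says.** Under Procedures and informed consent, complications are screened before randomization: "the definitive inclusion takes place if patients are going home after three days post-surgery and no complications are present". Then: "After the definitive inclusion, the baseline measurement and randomization take place". For the period afterwards the same section says: "The researcher can decide to withdraw a patient during the study for urgent medical reasons, such as thrombosis, infections of the knee or other complications". The wording is withdrawal of the patient, not stopping of the program or the device. The article does not say whether TUG, KOOS or SF-36 measurement continues.

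Under Statistical analysis, Primary and secondary outcomes: "The analyses will be performed following the intention-to-treat principle". The TUG is analysed "using generalized estimating equations (GEE) with an exchangeable correlation structure", and the continuous secondary outcomes in the same way. On missing data the section says: "Because GEE can adequately handle missing values (<20%), no imputation technique is planned on beforehand". It gives no assumption about why values are missing. Sample size adds: "Assuming a dropout rate of 15% a total number of 110 patients is needed".

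**The concern.** Two statements work against each other. The withdrawal rule acts after randomization and selects on events (thrombosis, knee infection, other complications) that plausibly go with slow recovery, so it can create missing TUG values related to the values themselves. The missing-data sentence then treats the amount missing as the test of adequacy. With 15% dropout expected, the trial would pass that test and nothing further would be done.

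Whether unweighted GEE is adequate depends on why data are missing. It is guaranteed consistent in general when missingness is unrelated to outcome given the model covariates. When missingness depends on observed outcomes (missing at random), it is close to unbiased only if its working covariance is about right. When missingness depends on unobserved outcomes, neither condition helps. At stake is the primary between-arm TUG comparison: if one arm loses more slow recoverers than the other, that arm looks better than it is.

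**Working it through.** **Reference effect.** Inputs from Sample size: N = 110, dropout 15%, SD 4.2, correlation 0.4, three follow-up visits. Neither the power nor the mean TUG behind the 10% difference is given, so 110 can be neither confirmed nor refuted, and the effect below is back-calculated.

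- Evaluable: 110 × 0.85 = 93.5, or 46.75 per arm.
- SD of a patient's three-visit mean: 4.2 × √[(1 + 2 × 0.4)/3] = 4.2 × √0.6 = 3.253 s.
- Two-sided 5%, 80% power (assumed): (1.960 + 0.842) × 3.253 × √(2/46.75) = 1.89 s.
- Range over other assumptions: 1.67 s (one-sided 5%, 80% power) to 2.18 s (two-sided, 90% power).

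**Simulation.** 55 per arm, three visits, SD 4.2, exchangeable correlation 0.4, no true effect, exchangeable GEE, 3,000 trials per scenario (Monte Carlo standard error about 0.012 s). In the first four rows half of the lost patients have no follow-up visit and half have week 2 only. In the last row all losses come after week 2. Outcome-related loss means that patients with a slower average TUG are more likely to be lost. The dropout splits are assumptions.

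| Loss mechanism | Dropout by arm | Bias (s) | Rejection rate |
|---|---|---|---|
| Unrelated to outcome | 20% vs 10% | about 0 | 6% |
| Outcome-related | 15% vs 15% | about 0 | 5% |
| Outcome-related | 18% vs 12% | 0.18 | 6.7% |
| Outcome-related | 20% vs 10% | 0.27 | 8% |
| Outcome-related | 25% vs 5% | 0.56 | 16% |
| Depends on observed week-2 TUG | 20% vs 10% | about 0 | 6% |

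The bias favours the arm that loses more slow recoverers. Against 1.89 s, the three biased rows are about 10%, 14% and 30%. The largest is 26% of 2.18 s and 34% of 1.67 s. Every row has about 15% dropout overall, so the 20% limit does not separate the safe rows from the biased ones.

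**Other covariance assumptions.** With SDs of 6, 4 and 2.6 s and correlations that fall with time, outcome-related loss gave 0.23 s (20% vs 10%) and 0.48 s (25% vs 5%). Loss depending on observed week-2 TUG gave up to 0.07 s. In another setting (SDs 6, 4 and 3 s, 15–17% dropout after week 2 depending on week-2 TUG differently by arm, 500 trials per scenario) GEE bias was 0.15–0.19 s, against about 0–0.04 s for a likelihood model with unstructured covariance. GEE bias under missing at random is thus about 0 to 0.2 s, depending on these assumptions.

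**Direct arithmetic.** Suppose complicated patients are 5–10 s slower and withdrawal differs by 5 percentage points (both assumed). Bias in the three-visit average is roughly difference × excess × share of visits lost:

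- lost before week 2: 0.05 × 5 = 0.25 s to 0.05 × 10 = 0.5 s;
- lost after week 2: two thirds of that, 0.17–0.33 s;
- lost after week 6: one third, 0.08–0.17 s.

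**The case against.** The other side has real points.

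- Nothing in the article suggests that complications differ by arm. Withdrawal is at the discretion of the researcher, and outcomes are measured by a blinded researcher, which makes allocation-driven withdrawal less likely. This stands as a limit on how probable the bias is. It does not cover a true difference in complications, or patients leaving by themselves in a trial where participants know their arm.
- A reader might infer that any difference in dropout passes straight into the result. It does not: unequal loss unrelated to outcome, and equal outcome-related loss, both gave bias of about zero.
- A reader might infer that the estimate describes only uncomplicated recoveries, or that the intention-to-treat statement is flatly contradicted. The article does not support this. GEE keeps each visit made before withdrawal in the randomized arm, patients with complications need not be withdrawn, and the article does not say that measurement stops.
- A reader might infer that withdrawn patients vanish from the cost comparison. Costs come from insurer and therapist records obtained with consent (Secondary outcomes, Healthcare use; Healthcare costs and cost-effectiveness), and nothing says these are lost on withdrawal.
- Follow-up after withdrawal can be a detail left to the full protocol. That is fair for silence alone. The 20% rationale, however, is a positive statement, and it is wrong.
- A mixed model or imputation under missing at random does not cure loss caused by an unobserved complication. This is correct and shapes the fix.

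**Conclusion.** The point holds as a risk of bias, not as a demonstrated one. The article gives a wrong reason for having no missing-data method, and its withdrawal rule can produce the kind of loss for which that reason fails. The between-arm TUG estimate is biased if outcome-related loss differs by arm: about 0.2 to 0.6 s for the splits examined, or roughly 10% to 30% of the 1.9 s implied at 80% two-sided power, with a false-positive rate of up to about 16% in the most extreme split. If loss depends only on observed TUG, GEE bias is smaller, about 0 to 0.2 s. The dropout splits, the slowness of complicated patients, the non-exchangeable covariances and the power are all assumptions; the article gives no complication rates. The point merits a change to the plan, since the repair is cheap.

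**What to change.** 1. In Procedures and informed consent, separate stopping the program or device from leaving follow-up. Patients with complications remain in measurement for TUG, KOOS and SF-36, and their cost records are still obtained, unless they withdraw consent. They are analysed as randomized. Clinical decisions are untouched.
2. In Primary and secondary outcomes, delete the under-20% rationale and state a missing-at-random assumption. Use a likelihood-based repeated-measures model with visit-specific variances, or multiple imputation before the GEE. Keep the planned GEE as a sensitivity analysis.
3. Add a sensitivity analysis for outcome-related missingness, for example delta-adjusted imputation for patients withdrawn for complications, because step 2 alone does not address that loss.

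Cost: a few extra visits and modest extra analysis. The article appeared on 5 July 2017 and recruitment was to end on 1 August 2017, so for patients already withdrawn step 1 can recover only visits still to come. That makes step 3 more important.
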